### Sample size

Power analyses were conducted with alpha = 0.05, power = 0.8, two-sided test, for within group and between group hypotheses. We assumed a correlation between time points = 0.5 and based on previous work (Gloster et al., 2015), a small to medium effect size was assumed. Required sample sizes were 75 individuals for within group research and 150 patients (75 per group) for between-group hypotheses. Taking missing values into account (ca. 10% dropout), the required sample size in order to have sufficient power for all three hypotheses was thus approximately 170 individuals. We therefore aim to recruit *n* = 85 patients per treatment modality.

### Participant recruitment and selection criteria

Participants are recruited from two specialized clinics practicing ACT (inpatient and outpatient) from ongoing referral and intake procedures. Since ACT is a transdiagnostic therapy which is efficacious for many disorders, and in order to increase generalizability within this effectiveness trial, selection criteria are purposefully kept to a minimum. Inclusion criteria are: Minimum 18 years of age, ability to speak German sufficiently, present for therapy and able to attend sessions, previous treatment (i.e., ≥ 20 sessions of empirically supported psychotherapy and/or minimum dosage and length of an approved drug as recommended by international guidelines), and sign a consent statement will be included the study. In addition, for patients in the out-patient setting, patients will also be included with < 20 sessions therapy experience to enable full modelling of patients from those without treatment experience, to those with treatment experience in the outpatient setting, to those with treatment experience in the inpatient setting. Exclusion criteria include acute suicidal intent, acute substance dependency, (where the primary treatment goal is detoxification), active mania, previous experience with ACT, and inability to read or complete assessments. Otherwise all diagnoses are included (i.e. Affective Disorders, Anxiety Disorders, Somatoform Disorders, Mood Disorders, Anxiety-stress related Disorders, Somatic Disorders, Obsessive-Compulsive Disorder, Impulse Control Disorders, Gambling Disorders, and Personality Disorders). When participants enter the clinic, medication is optimized when necessary, as determined by the attending physician in consideration of patient preference. Medication is then held constant throughout the intensive treatment phase.

### Outcome assessments

Assessments in questionnaire and interview format will occur at six primary time points to capture changes that the patients choose in the following domains: Therapy expectancy, psychological flexibility, social interactions, therapy consistent skills, well-being, emotion regulation, symptomatology, stress, and prosocial behavior. ESM will target the same domains. Table 1 shows a brief description of the assessments. Assessments are done by psychology graduates and doctoral students. Assessors are trained to competency and supervised regularly. All utilized assessments were chosen based on covering the respective domain and adequate quality criteria.

**Table 1 Tab1:** Description of assessment instruments of the Choose Change study

Abbreviation	Description
CEQ	The **Credibility and Expectancy Questionnaire** [50] is a 6-item scale for measuring treatment expectancy and rationale credibility for use in clinical outcome studies. There are two rating scales, one from 1 to 9 and another (Item 4) from 0 to 100%.
AAQ-II	The **Acceptance and Action Questionnaire** [51] is a 10-item self-report measure of psychological flexibility and acceptance. Each item is rated on a 7-point scale from 1 (never true) to 7 (always true).
PF	The **PsyFlex** [42] is a self-developed 6-item self-report measuring the process of Psychological Flexibility. Each item is rated on a 5-point scale from 1 (very often) to 5 (very rarely).
BAT	The **Behavioral Avoidance Test: Radiant Heat Induction Test** [52]**.** Thermal testing is performed by applying a thermode on the patient’s skin. A patient’s response to temperature stimuli (the sensory thermal threshold) is recorded.
OSS-3	The **Oslo Social Support Scale** [53] is a 3-item self-report measure of social support. Item 1 is rated on a 4-point scale, items 2 and 3 are assessed on a 5-point scale.
SIS	The **Social Interaction Scale** is a self-designed 3-item self-report measuring the frequency, duration, and discomfort of social interactions in the last 24 h. Item one is rated on a 4-point scale, item 2 on a 3-point scale.
RAS	The **Relationship Assessment Scale** [54] is a 7-item self-report measure of relationship satisfaction. Each item is rated on a 7-point scale from 1 (low satisfaction) to 5 (high satisfaction). Items 4 and 7 are reverse scored.
SNQAS	The **Social Network Quality and Action Scale** is a self-developed 10-item scale measuring the relationship quality with important people in a person’s life. In item 1, up to 15 people can be listed, Items 2–10 are assessed individually for every person mentioned in item 1. Items 2 and 3 specify the relation with the person concerned. Of the following items, 4 are rated on a 7-point scale, 2 on a 5-point scale and 1 on a 4-point scale.
CFQ	The **Cognitive Fusion Questionnaire** [55] is a 7 item self-report measure of cognitive fusion. Each item is assessed on a 7-point scale from 1 (never true) to 7 (always true).
FFMQ-SF	The **Five Facet Mindfulness Questionnaire – Short Form** [56] is a 24-item self-report measure of different aspects of mindfulness. Each item is measured on a 5-point scale from 1 (never applies) to 5 (always applies).
VLQ	The **Valued Living Questionnaire** [57] is a 2-item self-report measure assessing valued living in 12 different life domains. Both items are assessed on a 10-point scale from 1 (not important) to 10 (very important).
WHODAS 2	The **World Health Organization Disability Assessment Schedule – 2** [58] is a 17-item self-report disability assessment with 7 domain-specific scores. Each item is rated on a 5-point scale from 1(no difficulty) to 5 (extreme difficulty or cannot do).
MHC-SF	The **Mental Health Continuum – Short Form** [59] is a 14-item self-report measure of emotional, social and psychological well-being. Each item is rated on a 6-point scale from 0 (never) to 5 (every day)
MLQ	The **Meaning in Life Questionnaire** [60] is a 10-item measure of meaning in life. Each item is assessed on a 7-point scale from 1 (absolutely untrue) to 7 (absolutely true).
DERS	The **Difficulties in Emotion Regulation Scale** [61] is a 36-item self-report measure of emotion dysregulation. Each item is rated on a 5-point scale from 1 (almost never) to 5 (almost always).
ASQ	The **Affective Style Questionnaire** [62] is a 20-item self-report measure of individual differences in emotion regulation. Each item is rated on a 5-point scale from 1 (not true of me at all) to 5 (extremely true of me).
SCID-I/Screener	The **Structured Clinical Interview for DSM-IV – Axis I disorders** [38] is a semi-structured interview guide that enables mental health professionals to make DSM-IV Axis I diagnoses.
Severity Scale	The **Anxiety Disorders Interview Schedule (ADIS) severity rating scale** [39] was utilized to rate the diagnoses on a scale from 0 (absent) to 8 (very severe)
BDI-SF	The **Beck Depression Inventory – Short Form** [63] is a 7-item self-report measuring severity of symptoms associated with depression. Each item is rated on a 4-point scale.
BSCL	The **Brief Symptom Checklist** [64] is a 53-item self-report measure. Each item is rated on a 5-point scale from 0 (not at all) to 4 (very strongly).
PSWQ	The **Penn State Worry Questionnaire** [65] is a 16-item self-report assessing the trait of worry. Each item is rated on a 5-point scale from 1 (not a tall typical of me) to 5 (very typical of me).
FQ	The **Fear Questionnaire** [66] is a 24-item self-report of phobia. Each item is rated on a scale from 0 to 8.
OCI-R	The **Obsessive-Compulsive Inventory – Revised** [67] is an 18-item self-report measure of obsessive-compulsive symptoms. Each item is rated on a point scale from 0 (not at all) to 4 (extremely).
SIAS	The **Social Interaction Anxiety Scale** [68] is a 20-item self-report measure of fears in general social interaction. Each item is rated on a 5-point scale from 0 (not at all) to 4 (extremely).
PSS	The **Perceived Stress Scale** [69] is a 14-item self-report measure of perceived stress in different situations. Each item is rated on a 5-point scale from 0 (never) to 4 (very often).
DSS	The **Daily Stress Scale** [70] is a 7-item self-report measure of perceived stress in different life domains. Each item is rated on a 7-point scale from 1 (little incriminating) to 7 (not affected)
DAP-PS	The **Developmental Assets Profile – Prosocial Subscale** [71] is an 8-item self-report measure of developmental assets linked to different indicators of well-being. Each item is rated on a 4-point scale from 1 (not at all or rarely) to 4 (extremely or almost always)
EVOS	The **Prosociality questionnaire** is a self-designed 9-item self-report asking about prosociality in partnerships and derived from prosocial principles [72]. Items 1, 6, 7, and 9 are rated on a 5-point scale. Items 2–5, and Item 8 are rated on a 3-point scale.
COOP	The **Cooperation Scale** [73] is a 13-item self-report measure of cooperation in social situations. Each item is rated on a 6-point scale from 1 (I don’t agree at all) to 6 (I totally agree).
SRAS	The **Self Report Altruism Scale** [74] is a 20-item self-report measure of altruistic behavior. Each item is rated on a 5-point scale from 1 (never) to 5 (very often).

*Note.* Full names of the instruments are printed in bold for a better overview

Primary outcome measures will target symptoms and general functioning. These are assessed using questionnaires completed by the patients using the Brief Symptom Checklist (BSCL; to assess symptoms), the World Health Organization Disability Assessment Schedule – 2 (WHODAS 2; to assess functioning), and the Mental Health Continuum – Short Form (MHC-SF; to assess well-being). Primary outcomes are measured at baseline, post, and 12 months following treatment. The MHC-SF is measured at all time points.

Secondary outcomes are included to assess additional domains, such as treatment context, social context, spreading of effects, follow-up, daily context, and behavioral measures (see Table 2 and Table 3). In addition, an experimental paradigm will be used to measure how psychological flexibility impacts patients’ behavioral response to experimentally induced discomfort (i.e., radiant heat pain). This radiant heat pain paradigm is commonly used in research [35, 36] and will be administered at baseline, post, and 12 months after treatment.

**Table 2 Tab2:** Overview of domains, constructs, assessments, and respective time points at which each assessment is administered

Choose Change: Assessment Overview								
Domain	Construct	Instrument/Paradigm	Assessment Time					
			BL	Post	FU-1	FU-4	FU-9	FU-12
Therapy Expectancy	Expectancy	Credibility and Expectancy Questionnaire (CEQ)	x					
Psychological Flexibility	Psychological Flexibility/ Emotional Avoidance	Acceptance and Action Questionnaire – II (AAQ-II)	x	x				x
	Process of Psychological Flexibility	PsyFlex (PF)	x	x	x	x	x	x
	Behavioral Test/Experiment	Behavioral Avoidance Test (BAT): Heat Induction Test	x	x				x
Social interactions	Overall Social Support	Oslo Social Support Scale (OSS-3)	x	x				x
	Social Interaction	Social Interaction Scale (SIS)	x^i^	x^i^	x	x	x	x^i^
	Relationship Satisfaction	Relationship Assessment Scale (RAS)	x^i^	x^i^		x		x^i^
	Social Network Quality	Social Network Quality and Action Scale (SNQAS)	x^i^	x^i^	x	x	x	x^i^
ACT-Skills	Cognitive Fusion	Cognitive Fusion Questionnaire (CFQ)	x	x				x
	Mindfulness	Five Facet Mindfulness Questionnaire - short version (FFMQ-FS)	x	x				x
	Values	Valued Living Questionnaire (VLQ)	x	x				x
Well-being	General Functioning	WHO Disability Assessment Schedule 2.0 (WHODAS 2)	x^p^	x				x
	Flourishing Mental Health/ well-being	Mental Health Continuum – Short Form (MHC-SF)	x^ip^	x^i^	x^i^	x^i^	x^i^	x^i^
	Meaning of Life	Meaning in Life Questionnaire (MLQ)	x	x				x
Emotion Regulation	Problematic Emotion Regulation	Difficulties in Emotion Regulation Scale (DERS)	x	x				x
	Emotion Regulation	Affective Style Questionnaire (ASQ)	x	x				x
Diagnosis/ Symptomatology	DSM Diagnostic Information	Structured Clinical Interview for DSM-IV (SCID-I/Screener)	x					
	Depression	Beck Depression Inventory – Fast Screen (BDI-FS)	x	x	x	x	x	x
	Problems and Discomfort	Brief Symptom Checklist (BSCL)	x^p^	x				x
	Worry (GAD)	Penn State Worry Questionnaire (PSWQ)	(x)	(x)		(x)		(x)
	Anxiety/Fear	Fear Questionnaire (FQ)	(x)	(x)		(x)		(x)
	Obsessions and Compulsions (OCD)	The Obsessive-Compulsive Inventory, short Version (OCI-R)	(x)	(x)		(x)		(x)
	Social Fear	Social Interaction Anxiety Scale (SIAS)	(x)	(x)		(x)		(x)
Stress	Perceived stress	Perceived Stress Scale (PSS)	x	x				x
	Daily stress	Daily Stress Scale (DSS)	x^i^	x^i^	x	x	x	x^i^
Prosocial Behavior	Prosocial Behaviors	Developmental Assets Profile – Prosocial Subscale (DAP-PS)	x	x				x
		Prosociality Questionnaire (EVOS)	x	x				x
	Cooperation	Cooperation Scale (COOP)	x	x				x
		The Self-Report Altruism Scale (SRAS)	x	x				x
Therapy Consistent Skills	Transfer of Skills to Daily Life	Vignettes			x	x	x	x

*Note.* BL = Baseline; FU-1, FU-4, FU-9, FU-12 = Assessments at 1-, 4-, 9-, and 12-month follow up; ESM = Event Sampling Methodology (smartphone); i = to be completed by close person in addition to patient; () = to be filled out only by patients who have that specific symptomatology (SCID); p = primary outcome measures

In order to test whether treatment context has an impact on patients’ well-being and functioning (i.e. flourishing) [37], ACT will be administered for both in- and outpatients. For inpatients, a multidisciplinary team is involved, consisting of psychotherapists providing individual and group therapy and the nursing and support staff providing ACT specialized sessions. For outpatients, psychotherapists provide individual ACT sessions. All psychotherapists are certified for this study through attendance of several ACT trainings and provision of a certification role play video rated by a certified ACT trainer. Therapists will make choices based on ACT skills and procedures, which will all be documented following each session. This allows for the documentation of ACT’s clearly defined skills, while enabling a flexible and situationally sensitive application.

#### Baseline: diagnostics, assessment

During the first week of therapy participants complete informed consent procedures before data collection. All participants complete the Structured Clinical Interview for DSM-IV Axis I Disorders (SCID) [38] to determine diagnostic status. Diagnoses are rated on the Anxiety Disorders Interview Schedule (ADIS) severity rating scale [39]. The diagnosis with the highest severity score determines the primary diagnosis. Following the SCID, participants complete diagnostic-specific and transdiagnostic questionnaires (see Table 2).

#### Post: assessment

At completion of the intensive therapy phase post assessment is done (i.e. diagnostic-specific and transdiagnostic questionnaires, ESM, and the heat induction test). Except for the SCID and the Credibility and Expectancy Questionnaire (CEQ) procedures and items will be the same as in baseline (see Table 2 and Table 3).

**Table 3 Tab3:** Overview of domains and respective time points at which each EMA assessment is administered

Choose Change: Assessment Overview			
Domains assessed	Assessment Time for ESM		
	BL	Post	FU-12
Therapy Expectancy			
Psychological Flexibility	x	x	x
Social interactions	x	x	x
ACT-Skills	x	x	x
Well-being	x	x	x
Emotion Regulation	x	x	x
Diagnosis/ Symptomatology	x	x	x
Stress	x	x	x
Prosocial Behavior	x	x	x
Therapy Consistent Skills			

*Note. BL* Baseline, *ESM* Event Sampling Methodology (smartphone), *FU-12* Assessments at 12-month follow up

#### Follow-up: 1, 4, 9, and 12 months after treatment

In order to assess what was learned during therapy and how psychological flexibility, well-being, and symptoms are associated with each other, patients stay in contact with the research team after completing the intensive inpatient or outpatient treatment phase. Over the following year, four follow-up appointments are conducted at 1, 4, 9, and 12 months after completion of the intensive therapy phase. Follow-up appointments include an online questionnaire and an interview. For the included questionnaires see Table 2.

### Assessments measuring mechanisms of action across levels of analysis

#### Behavioral approach test

A heat induction test (using the TSA-II, [40]) was used in order to test how participants respond to an uncomfortable and ambiguous stimulus not subject to the same demand characteristics as questionnaires. During this test, temperature increases until the patient stops the increase with a click of the mouse. This temperature is then held constant to test tolerance. This test is administered at Baseline and Post (to determine whether the tolerance changes during treatment) and at Follow-Up 12 (to determine whether the tolerance changes after treatment). Before and after participants will complete a pain-related questionnaire.

#### Weekly psychological flexibility process measure (between baseline and post)

In order to examine whether patients with higher levels of psychological flexibility will profit faster from treatment, weekly psychological flexibility progression will be measured during the intensive treatment phase (between Baseline and Post). For this, the PsyFlex [41, 42] will be used across different information sources. The PsyFlex is a self-developed instrument which aims at measuring state psychological flexibility through capturing all six skills of the ACT Hexaflex [43]. The PsyFlex is filled out by the patients, their therapists, and – in the inpatient setting – their nurse, which results in an evaluation of one person from up to three different perspectives.

#### Ambulatory monitoring (ESM at baseline, post, and 12 months after treatment)

In order to examine how psychological flexibility and other treatment parameters were applied to stressors in real-time in the participants’ natural environment, how social group interactions affected the individual, and how these aspects changed over time, patients receive a smartphone from the research team and instructions on its usage (i.e. operation of the smartphone, recognition of the signaling tone, answer example questions). Data will be collected at Baseline, Post, and Follow-Up 12. At each time point, patients will carry the smartphone for one week, using a signal-contingent ESM approximately every three hours (e.g., 8 am, 11 am, 2 pm, 5 pm, 8 pm, and 11 pm). Items stem from previous ESM studies [44–47] and are based on a functional analysis of social interactions [48] due to their individual nature. In addition to the data assessed via questionnaires, GPS data (e.g. time-stamped data regarding location, speed of travel if travelling, and time spent at different locations) of the patients will be collected during the respective ESM week. For assessed domains within the ambulatory assessement, see Table 3.

#### Close person (baseline, post, and 12 months after treatment)

In order to investigate the impact of the social context, patients are asked to give the research team permission to contact a person of their choice, who is close to them. This close person is then contacted by the research team. After obtaining informed consent from this close person, an online questionnaire is completed at Baseline, Post, and at Follow-Up 12 by the close person, providing information about their relationship and well-being. For the included questionnaires see Table 2.

#### Therapy integrity

Therapy will consist of an intensive treatment phase lasting approximately twelve treatment sessions. Therapists will be certified for this study. Therapy sessions will be recorded and of those, two will be randomly selected and rated by external and independent ACT experts to assess treatment integrity. Therapy integrity will be further promoted via regular targeted supervision sessions by ACT experts.

### Analysis plan

For all analyses we will use multilevel models with time as level 1 and person as level 2 variables. These models are able to deal with the interdependence of observations across time within the same subject. Hypothesis 1 refers to a multilevel model with time as within-subjects variable and no between-subjects variable. Hypothesis 2 is based on hypothesis 1 but will contain in addition one between-subjects factor (group, 2 levels), plus the interaction between time and group, which is our primary focus. Hypothesis 3 refers to a multilevel model with social stress as predictor and psychological flexibility as mediator. Again, we will be interested in the interaction between these two characteristics, which are both time-varying within subjects.

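### The H2 model compares two non-randomised settings with no adjustment for diagnosis, severity or treatment history, so differences in course tied to case mix would be read as a setting effect

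*Protocol article*

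**What the plan says.** The protocol article, Analysis plan, gives the Hypothesis 1 model as time within persons with no between-subjects variable. The Hypothesis 2 model builds on it and "will contain in addition one between-subjects factor (group, 2 levels), plus the interaction between time and group, which is our primary focus". The article names no covariate, stratification or weighting.

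Participant recruitment and selection criteria says that patients come from an inpatient and an outpatient clinic through their usual referral and intake. Nearly all diagnoses are eligible. Previous treatment is required, either at least 20 sessions of psychotherapy or adequate drug treatment, but outpatients may also enter with fewer than 20 sessions.

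Baseline: diagnostics, assessment has every participant interviewed with the SCID and the diagnoses rated on the ADIS severity scale (0 to 8). "The diagnosis with the highest severity score determines the primary diagnosis". Under Outcome assessments, "Primary outcomes are measured at baseline, post, and 12 months following treatment"; the MHC-SF is also measured at the other follow-ups.

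**The concern.** The article presents setting as a treatment context whose effect can be tested. When setting follows the route of referral, the two groups can differ in diagnosis, severity and treatment history, and any of these can govern how fast a patient improves or how well gains are kept. With setting as the only between-subjects term, the interaction absorbs all such differences.

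The direction is not known. If inpatients are more severely ill and more severely ill patients change more, the inpatients appear to do better and the disadvantage predicted by H2 is masked. If severe or long-treated patients change less, the model produces the predicted disadvantage with no contribution from setting. Either way, the test named as the primary focus would not answer the question put to it, although the variables needed to reduce the problem are established at entry.

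**Working it through.** **Inputs from the article (Sample size).** "Power analyses were conducted with alpha = 0.05, power = 0.8, two-sided test"; "We assumed a correlation between time points = 0.5"; "a small to medium effect size was assumed", with no number; "150 patients (75 per group) for between-group hypotheses"; about 10% dropout; target 85 per setting.

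**The plan's own figure.** 150 / 0.9 = 167 (or 150 x 1.1 = 165), which agrees with the stated total of approximately 170. The 75 per group cannot be computed forward without a numeric effect size. Solving backwards, the SD of a change score is sqrt(2(1 - 0.5)) = 1 outcome SD. The standard error of the difference in mean change is sqrt(2/75) = 0.163. By the noncentral t with 148 df, 80% power needs 2.82 x 0.163 = 0.46 SD. That effect is implied by the sample size, not stated.

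**What cancels.** Take baseline as one of the time points and time as categorical. Time x setting is then the difference in mean change, and a constant gap between settings drops out. In 4,000 simulated trials with 75 per group, correlation 0.5 and a stable gap of 0.5 or 0.8 SD, the mean interaction was 0.00 and the test rejected 4% to 5% of the time.

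**What does not cancel.** Let D be the severity difference between settings in SD, and r the within-setting correlation of severity with change. Both are assumptions. With no setting effect, the expected interaction is b = r x D (in change SD, here equal to outcome SD). The rejection probability is 1 - Phi(1.96 - b/0.163) + Phi(-1.96 - b/0.163).

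| D | r | b | b as share of 0.46 | Rejection at nominal 5% |
|---|---|---|---|---|
| 0.2 | 0.1 | 0.02 | 4% | 5.2% |
| 0.2 | 0.5 | 0.10 | 22% | 9.4% |
| 0.5 | 0.2 | 0.10 | 22% | 9.4% |
| 0.5 | 0.3 | 0.15 | 33% | 15% |
| 0.8 | 0.3 | 0.24 | 52% | 31% |
| 0.8 | 0.5 | 0.40 | 87% | 69% |

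**Precision after adjusting for severity.** The variance relative to the unadjusted contrast is (1 - r^2)(1 + D^2/4):
- D = 0.5, r = 0.5: 0.75 x 1.0625 = 0.80, a gain.
- D = 0.5, r = 0.2: 0.96 x 1.0625 = 1.02, a slight loss.
- D = 0.8, r = 0.2: 0.96 x 1.16 = 1.11, a loss.

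**Adjusting for the baseline outcome instead.** With balanced baselines, the variance falls from 2(1 - 0.5) = 1.00 to 1 - 0.25 = 0.75, and power at 0.46 SD rises from 80% to 90%. If each setting has its own stable mean, however, this model creates a false setting effect of (1 - 0.5)D: 0.25 SD at D = 0.5 and 0.40 SD at D = 0.8 (D now being the baseline gap). In the same simulations it rejected 40% and 74% of the time.

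**The case against.** **Baseline is already in the model.** A reader might infer that any severity difference between settings biases the H2 test. It does not: a stable difference cancels from the interaction. This stands, subject to one gap in the text. The Analysis plan does not say whether baseline is a time point for H2, whose wording under Main research areas concerns the follow-up period. If H2 were judged on levels during follow-up, a level difference would enter directly.

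**The regression-to-the-mean figures are a ceiling.** With a 0.5 SD baseline gap and full regression to a common mean, the spurious difference in change is 0.25 SD. The test then rejects 33% of the time, and power against a true 0.46 SD inpatient disadvantage falls from 80% to about 25%. This requires selection on the baseline score itself, whereas patients are referred before the baseline questionnaires. If selection acts on severity at referral and every pair of time points correlates 0.5, the gap is the same at baseline and later, and the artefact is zero. This also stands. It disposes of regression to the mean as an expected bias, but not of a course that differs by diagnosis, severity or treatment history.

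**Precision.** A reader might infer that leaving out covariates costs power in general. The calculations do not support that. The gain from 80% to 90% needs balanced baselines and a model that is itself biased under a stable gap, and a weakly predictive, imbalanced covariate lowers precision.

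**The article is a summary.** A covariate list could sit in a fuller plan. But the article does more than stay silent: it specifies no between-subjects variable for H1 and one for H2. If a fuller plan adds covariates, the two texts need to be reconciled.

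**Prior treatment is the clearer confounder.** Agreed. It is the one difference between settings that the article itself builds in, and it belongs in the model.

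**Conclusion.** The point holds as a matter of bias. As written, the H2 model attributes to setting any difference in course that comes from diagnosis, severity or treatment history. How large this is cannot be derived from the article. Over the assumed range the false-positive rate runs from essentially nominal (5%) to 69%, with 15% at a middle value, so the problem may be negligible or serious. The rates rest on 75 analysed per group, a correlation of 0.5 between time points, a difference-in-change reading of the interaction and a normal approximation.

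The article does not show that inpatients enter more severely ill, that any particular bias is present, or that the unadjusted model is generally less precise. It also does not support replacing the stated contrast with one adjusted for the baseline outcome, since that model has a failure case of similar size. Adjustment reduces the problem but cannot make the comparison causal: outpatients who do not meet the previous-treatment criterion have no inpatient counterpart, so for them history and setting cannot be separated.

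**What to change.** In the Analysis plan for Hypothesis 2:

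1. Add broad primary-diagnosis group (SCID), ADIS severity of the primary diagnosis, and previous treatment, each with its interaction with time. Keep time x setting as the term of interest, and state whether baseline is one of the time points.
2. As a sensitivity analysis, repeat the comparison without the outpatients admitted only under the relaxed rule for fewer than 20 sessions. Define this group by the previous-treatment criterion as a whole, because an inpatient can qualify through drug treatment.
3. Word the H2 conclusion as an association with setting.
4. If a model adjusted for the baseline outcome is wanted, show it only as a further sensitivity analysis, and state that it is biased when each setting has its own stable mean.

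The cost is wording and a small number of extra models. SCID diagnosis and ADIS severity are collected at baseline, and previous treatment has to be established to apply the eligibility rule. The downsides are a few degrees of freedom, the need to group diagnoses into broad classes, and possibly slightly lower precision if the covariates are imbalanced and only weakly predictive.

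### The Hypothesis 2 model uses a two-level setting factor although the prior-treatment criterion is waived for outpatients only, so setting is confounded with meeting that criterion

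*Protocol article*

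**What the plan says.** **Eligibility** (Protocol article, Participant recruitment and selection criteria). Previous treatment is an inclusion criterion. It is met by at least 20 sessions of empirically supported psychotherapy and/or an approved drug at guideline dose and duration. For outpatients alone, entry is also open to patients with fewer than 20 sessions. The stated reason is "to enable full modelling of patients from those without treatment experience, to those with treatment experience in the outpatient setting" and on to experienced inpatients, which makes three strata.

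**Source of patients** (same section). "Participants are recruited from two specialized clinics practicing ACT (inpatient and outpatient) from ongoing referral and intake procedures". No random allocation to setting is described.

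**Model** (Analysis plan). Hypothesis 2 extends the Hypothesis 1 model by "one between-subjects factor (group, 2 levels), plus the interaction between time and group, which is our primary focus". The paragraph names no third level, no prior-treatment term and no restriction of the sample.

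**Interpretation** (Study aims; Main research areas). The inpatient-outpatient difference is presented as an effect of the social context of treatment setting.

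**Size** (Sample size). "Required sample sizes were 75 individuals for within group research and 150 patients (75 per group) for between-group hypotheses", with "We assumed a correlation between time points = 0.5".

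**The concern.** The two sections do not fit together. Outpatient entry was widened so that three strata could be modelled, and a factor with two levels cannot represent three strata. As written, the patients admitted under the waiver are averaged into the outpatient arm, and the inpatient arm can contain nobody admitted on those terms.

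If patients who do not meet the criterion follow a different course from those who do, part of the group-by-time term reflects the entry rule and not the setting. That term is the declared primary focus of Hypothesis 2. The study could then report a setting effect where there is none, or mask one that exists.

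**Working it through.** **Inputs from the article (Sample size).** Two-sided alpha 0.05, power 0.80, correlation between time points 0.5, 75 evaluable patients per group, about 10% dropout. The effect size is described only as small to medium, without a number.

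**Reproducing the plan's figure.** 75 / (1 − 0.10) = 83.3, so 84 per group; 150 / (1 − 0.10) = 166.7, so 167. Both agree with the planned 85 per setting and about 170 in total. The base of 75 per group can only be solved backwards, because no numeric effect size is given.

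**Assumptions, not in the article.** p is the share of outpatients who do not meet the prior-treatment criterion. D is their difference in change over time, in SD units, from patients who do meet it.

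**Bias.** Let patients who meet the criterion change by m as outpatients and by m + S as inpatients, where S is the true setting effect.

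- Mean change, outpatient arm: (1 − p)·m + p·(m + D) = m + pD
- Mean change, inpatient arm: m + S
- Two-level contrast, inpatient minus outpatient: S − pD

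The contrast is therefore off by p × D in absolute size, and its sign depends on D. If D = 0 there is no bias.

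**Consequence when S = 0.** I use a two-point change score as a simplification.

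- SD of change = √(2 × (1 − 0.5)) = 1 SD
- SE = √(1/75 + 1/75) = 0.163
- Rejection probability = P(Z > 1.96 − pD/SE) + P(Z < −1.96 − pD/SE)
- p = 0.5, D = 0.3: shift 0.15, ratio 0.92, rejection about 15%
- p = 0.5, D = 0.5: shift 0.25, ratio 1.53, rejection about 33%

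Over a wider set of assumed values:

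| Share p | D = 0 | D = 0.2 | D = 0.3 | D = 0.5 |
|---|---|---|---|---|
| 0.25 | 5% | 6% | 7% | 12% |
| 0.50 | 5% | 9% | 15% | 33% |
| 0.75 | 5% | 15% | 28% | 63% |

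A simulation of 10,000 trials per case with p = 0.5 gave 15.3% (D = 0.3) and 32.7% (D = 0.5) for the two-level contrast. With the three strata modelled, the rate was 5.1% and 5.2%.

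**Price of separating the strata.** The setting contrast becomes 75 inpatients against 75 × (1 − p) outpatients who meet the criterion. At p = 0.5 this is 75 against 38:

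- SE = √(1/75 + 1/38) = 0.199, against 0.163
- Difference detectable with 80% power (noncentral t): 0.56 SD, against 0.46 SD
- Power at 0.46 SD: 63%, against 80%

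**The case against.** The Analysis plan is one short paragraph that gives each model's skeleton. Covariates and sensitivity analyses are commonly left to a fuller document. The eligibility section does not say that Hypothesis 2 is the analysis meant to use the three strata, and the Discussion expects several publications, so experience could be modelled elsewhere. This has weight against any claim that the plan has no covariates at all. A reader might infer that from the paragraph's silence, but the article does not say it. It does not remove the point, because the paragraph does fix the between-subjects part of Hypothesis 2 as one factor with two levels and names its interaction with time as the focus. Analysing experience in another paper would not repair that contrast.

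A reader might also infer that no inpatient can have fewer than 20 sessions, so that setting is confounded with session count. The documents do not support this. The criterion is joined by and/or, so an inpatient may qualify by drug treatment alone. The waiver, for its part, covers partly treated as well as untreated outpatients. The confounding is with meeting the criterion.

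A further tempting step is to say that severity and diagnosis differ between the settings, and to ask for baseline symptom score by time and diagnosis by time terms. The article reports no such difference. The Brief Symptom Checklist is a primary outcome whose baseline is itself a time point in the model, so it would stand on both sides. Diagnosis by time would be sparse with about 150 evaluable patients and some ten listed categories.

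Finally, p and D are assumed, and the working uses two time points although the planned models may use more. This limits the figures, not the structure.

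**Conclusion.** The concern holds as a mismatch between the eligibility section and the Analysis plan. The stated Hypothesis 2 contrast estimates setting together with any difference in course of outpatients who do not meet the prior-treatment criterion.

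The bias is p × D, and the documents give neither quantity. Its size and direction are unknown, and it vanishes if prior treatment does not change the course. The 15% to 33% false-positive rate is an illustration for p = 0.5 and D = 0.3 to 0.5 SD, with 75 per group and a two-point change score. It is not a forecast. A reader might infer that the setting result will be wrong; the article does not support that. What it shows is that the model as specified cannot tell the two explanations apart, although patients who meet the criterion exist in both settings and a simple change would separate them. Severity: should be fixed.

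**What to change.** In the Analysis plan, replace the two-level group factor in Hypothesis 2 by the three-level factor announced in the eligibility section. Equivalently, add criterion status and its interaction with time; a main effect of status alone would not adjust the group-by-time term. Define the strata by whether the prior-treatment criterion is met, by sessions and/or drug treatment, and not by session count. Take the setting contrast as inpatients against outpatients who meet the criterion. Report the pooled two-level contrast as a sensitivity analysis.

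State also that what remains is a non-randomised difference of setting plus clinic: there is one clinic per setting, and inpatients additionally receive group therapy and ACT sessions from nursing and support staff (Outcome assessments).

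**Cost.** The change is to the wording of the analysis. Criterion status has to be established to apply the entry rules, but it is not listed in Table 2, so the sponsor should confirm that it is recorded for every outpatient. The setting contrast loses precision, as the working shows for an assumed share of one half, and the loss grows with the share. The expected share should therefore be stated beside the sample size.
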